#### 7.1.4 Data Conventions

① **Missing dates:** if previous dates are incomplete and affect subsequent date calculations, impute as follows without contradiction to other dates:

➤ **Dates related to AEs**

- ✓ Missing day, month and year of AE onset date: the date will not be imputed and is missing;
- ✓ Missing day and month of AE onset date: if the "year" of the onset date is the same as the "year" of the first dose date, impute as the first dose date; if the "year" of the onset date is early than the "year" of the first dose date, impute 31 December; if the "year" of the onset date is later than the "year" of the first dose date, impute 1 January.
- ✓ Missing day of AE onset date: if the "month and year" of the onset date are the same as the "month and year" of the first dose date, impute as the first dose date; if the "month and year" of onset date are early than the "month and year" of the first dose date, impute with the last day of the month; if the "month and year" of onset date are later than the "month and year" of the first dose date, impute with 1 as the day.
- ✓ Missing hour and minute of AE onset date: if the "day, month and year" of onset date are the same as those of the first dose date, impute as the hour and min of the first dose date; if the "day, month and year" of onset date are early than those of the first dose date, impute 23:59; if the "day, month and year" of onset date are later than those of the first dose date, impute 00:00.
- ✓ Missing minutes of AE onset date: if the "hour and day, month and year" of the onset date are the same as those of the first dose date, impute with the minutes of the first dose date; if the "hour and day, month and year" of onset date are early

than those of the first dose date, impute 59 as the minutes; if the "hour and day, month and year" of onset date are later than those of the first dose date, impute 0 as the minute.

- ✓ Missing day, month and year of AE end date: the end date will not be imputed and will be considered as missing.
- ✓ Missing day and month of AE end date: the end date will be imputed with 31 December.
- ✓ Missing day of AE end date: impute as the last day of the month.

➤ **Dates related to concomitant medications**

- ✓ Missing day, month and year of start date of concomitant medication: the date will not be imputed and is missing;
- ✓ Missing day and month of start date of concomitant medication: if the "year" of the start date is the same as the "year" of the first dose date, impute as the first dose date; if the "year" of the start date is early than the "year" of the first dose date, impute 31 December; if the "year" of the start date is later than the "year" of the first dose date, impute 1 January.
- ✓ Missing day of start date of concomitant medication: if the "month and year" of the start date are the same as the "month and year" of the first dose date, impute as the first dose date; if the "month and year" of start date are early than the "month and year" of the first dose date, impute with the last day of the month; if the "month and year" of start date are later than the "month and year" of the first dose date, impute with 1 as the day.
- ✓ Missing hour and minute of start date of concomitant medication: if the "day, month and year" of start date are the same as those of the first dose date, impute as the hour and min of the first dose date; if the "day, month and year" of start date are early than those of the first dose date, impute 23:59; if the "day, month and year" of start date are later than those of the first dose date, impute 00:00.
- ✓ Missing minutes of start date of concomitant medication: if the "hour and day, month and year" of the start date are the same as those of the first dose date,

impute with the minutes of the first dose date; if the "hour and day, month and year" of start date are early than those of the first dose date, impute 59 as the minutes; if the "hour and day, month and year" of start date are later than those of the first dose date, impute 0 as the minute.

- ✓ Missing day, month and year of end date of concomitant medication: the end date will not be imputed and will be considered as ongoing.
- ✓ Missing day and month of end date of concomitant medication: the end date will be imputed with 31 December.
- ✓ Missing day of end date of concomitant medication: impute as the last day of the month.

② **Baseline** is defined as the last non-missing data before the first dose.

③ **Change from baseline** is defined as the test value at follow-up visit after treatment - baseline value.

④ **Data derivation and conversion:**

Age: in years, = (date of informed consent - date of birth)/365.25, rounded down.

## 7.2 Study Population

### 7.2.1 Case Distribution

Description of subject enrollment, dropouts, and removals from PPS at each site: number and percentage;

Subject disposition for each dataset: subject disposition will be summarized for each analysis population.

Subjects who drop out will be described one by one: medication, reason for dropout, etc.

Subjects who are removed from each analysis population will be listed (including protocol deviations and reasons for exclusion).

### 7.2.2 Protocol Violations

Protocol violations will be summarized and described.

### 7.2.3 Analysis of Subject Characteristics

Age: mean, standard deviation, maximum, minimum and median will be used to describe the age;

Sex: frequency and constituent ratio will be calculated;

Ethnicity: frequency and constituent ratio will be calculated;

Height, weight, and body mass index (BMI): mean, standard deviation, maximum, minimum and median will be used;

CYP2D6, CYP3A4 and CYP3A5 genotypes: frequency and constituent ratio will be calculated according to metabolic phenotype;

ASA classification: frequency and constituent ratio will be calculated;

Past medical history and comorbidities, surgical history, smoking, alcohol consumption and allergy history: frequency and constituent ratio will be calculated;

Surgery: frequency and constituent ratio will be calculated according to the method of anesthesia, and  $\chi^2$  test will be used for comparison between groups; surgery time will be described using mean, standard deviation, maximum, minimum and median;

Whether sufentanil is given intravenously to prevent breakthrough pain: frequency and constituent ratio will be calculated;

Baseline NRS scores: mean, standard deviation, maximum, minimum and median will be used to describe the scores;

Baseline vital signs (blood pressure, respiratory rate, heart rate, body temperature)/oxygen saturation (SpO2): mean, standard deviation, maximum, minimum and median will be used;

Baseline physical examination: frequency and constituent ratio will be calculated for the assessment results of each parameter;

Baseline electrocardiogram: heart rate, PR, QT and QTc intervals will be described using mean, standard deviation, maximum, minimum and median; frequency and constituent ratio will be calculated for ECG assessment results;

Infectious disease screening and drug abuse screening: the frequency and constituent

ratio of the assessment results of each indicator will be calculated.

### 7.3 Efficacy Evaluation

#### 7.3.1 Analysis of Primary Efficacy Variable

- Time-weighted Sum of Pain Intensity Differences at rest up to 24 h after starting infusion of loading dose of investigational product (SPID24).

The calculation formula is as follows:  $SPID_t = \sum PID_t * (TIME_t - TIME_{t-1})(h)$ , e.g.  $SPID_2 = (PI_2 - PI_0) \times (2-1) + (PI_1 - PI_0) \times (1-0.5) + (PI_{0.5} - PI_0) \times (0.5-0)$ .

Note: calculations will be performed using the planned time points.

Mean, standard deviation, maximum, minimum, and median will be used to describe SPID24 in each group. Sequential tests will be performed between the groups: the test between the high dose group and the placebo group will be performed first with  $\alpha$  of 0.05 (two-sided). If there is a significant difference between the high dose group and the placebo group, then the test between the low dose group and the placebo group will be performed with  $\alpha$  of 0.05 (two-sided); if there is no significant difference between the high dose group and the placebo group, only exploratory analysis will be performed for the comparison of the low dose group and the placebo group.

A group t-test will be used for the comparison between two groups, and the difference in SPID24 between the two groups and its 95% CI will be calculated.

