### Efficacy Variables

#### Primary Efficacy Variable

Time-weighted Sum of Pain Intensity Differences at rest up to 24 h after starting infusion of loading dose of investigational product (SPID24).

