After randomization, the investigator should infuse the investigational product to the subject as soon as possible (within 15 min after the randomization). The loading dose of the investigational product will be 5 mL, administered by an infusion pump, and the intravenous infusion time will be approximately 10 min. The Patient Controlled Analgesia (PCA) pump containing the investigational product can be initiated approximately 30 min after the start of infusion of the loading dose. The subject can receive 1 mL of the investigational product at a single press of PCA pump, and the minimum interval between two adjacent effective presses is 10 minutes. The subject will continue using the PCA pump until 24 h ( $\pm$  5 min).

After the end of loading dose infusion, rescue analgesia may be given if the investigator determines that the investigational product can not meet the subject's analgesic needs (NRS  $\geq$  4 points). The first choice of rescue analgesics is parecoxib sodium for injection (20 mg for the first intravenous injection, followed by additional doses as needed, with a total dose of not more than 80 mg over 24 h), and sufentanil injection (2.5 µg for a single intravenous injection) can be used after reaching the maximum cumulative dose of parecoxib sodium for injection.

After randomization, the investigator will instruct the subject to assess the NRS score at rest within 5 minutes prior to the start of infusion of loading dose as baseline. The investigator will

instruct the subject to assess the NRS scores at rest immediately after the end of loading dose infusion and 20 min, 30 min, 45 min ( $\pm 1$  min as the assessment point window from immediately after the end of loading dose infusion to 45 min), 1 h, 1.5 h, 2 h, 3 h, 4 h, 5 h, 6 h ( $\pm 5$  min as the assessment point window from 1 h to 6 h), 8 h, 10 h, 12 h ( $\pm 10$  min as the assessment point window for 8 h, 10 h, and 12 h), 18 h, and 24 h ( $\pm 20$  min as the assessment point window for 18 h and 24 h) after the infusion. At the same time as each assessment of NRS score, the investigator will instruct the subject to assess the degree of pain relief (PR) using the Likert scale (0 as no response, 1 mild response, 2 moderate response, 3 significant response, 4 complete response).

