#### **Rescue Treatments**

After the end of loading dose infusion of the investigational product, parecoxib sodium for injection will be first used as a rescue analgesic if the investigator determines that the investigational product can not meet the subject's analgesic needs ( $\text{NRS} \geq 4$  points). Dose of parecoxib sodium for injection: 20 mg will be injected intravenously for the first time, followed by additional doses as needed, with a total dose of not more than 80 mg over 24 h. Sufentanil injection (2.5 µg for a single intravenous injection) can be used after reaching the maximum cumulative dose of parecoxib sodium for injection. Rescue analgesics should be truthfully documented in the original records and eCRFs. After the treatment period, the subject's

subsequent analgesics and dosages will be at the discretion of the investigator according to the hospital's routine practices.

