## **Evaluation**

### **Efficacy Evaluation**

- **SPID evaluation:** the investigator will instruct the subjects to assess the pain intensity (PI) at rest using the Numeric Rating Scale (NRS, 0-10 for varying degrees of pain, 0 for painlessness, larger numbers for more severe pain, and 10 for the worst pain) and obtain the PI score. The specific assessment points are: after randomization and within 5 min before the start of infusion of loading dose of investigational product (as baseline), immediately after the end of loading dose infusion, 20 min, 30 min, 45 min ( $\pm 1$  min as the assessment point window from immediately after the end of loading dose infusion to 45 min), 1 h, 1.5 h, 2 h, 3 h, 4 h, 5 h, 6 h ( $\pm 5$  min as the assessment point window from 1 h to 6 h), 8 h, 10 h, 12 h ( $\pm 10$  min as the assessment point

window for 8 h, 10 h, and 12 h), 18 h and 24 h ( $\pm 20$  min as the assessment point window for 18 h and 24 h) after the infusion. The difference from baseline PI score will be recorded as PID, calculated using the formula  $SPID_t = \sum [PID_t * (TIME_t - TIME_{t-1})](h)$ . For example,  $SPID_2 = (PI_2 - PI_0) \times (2-1) + (PI_1 - PI_0) \times (1-0.5) + (PI_{0.5} - PI_0) \times (0.5-0)$ .

- **TOTPAR evaluation:** the investigator will instruct the subject to assess the degree of pain relief (PR) using the Likert scale (0 as no response, 1 mild response, 2 moderate response, 3 significant response, 4 complete response) and obtain the PR score. The specific assessment points are: immediately after the end of loading dose infusion and 20 min, 30 min, 45 min ( $\pm 1$  min as the assessment point window from immediately after the end of loading dose infusion to 45 min), 1 h, 1.5 h, 2 h, 3 h, 4 h, 5 h, 6 h ( $\pm 5$  min as the assessment point window from 1 h to 6 h), 8 h, 10 h, 12 h ( $\pm 10$  min as the assessment point window for 8 h, 10 h, and 12 h), 18 h and 24 h ( $\pm 20$  min as the assessment point window for 18 h and 24 h) after the infusion. TOTPAR is calculated according to the formula  $TOTPAR_t = \sum [PR_t * (TIME_t - TIME_{t-1})](h)$ .
- **Evaluation of analgesia by the investigational product:** record the total number of presses and number of effective presses of PCA pump from 0 h to 24 h.

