### **Data Analysis/Statistical Method**

#### **Sample Size**

With reference to the results of the foreign study TRV130-3002, assuming that the primary efficacy variable SPID24 in the SHR8554 0.75 mg group in this study is comparable to the efficacy in the 0.35 mg group in the TRV130-3002 study, and conservatively assuming that the mean (standard deviation) of SPID24 in the low dose group of this study is 88 (45), and the mean (standard deviation) of SPID24 in the placebo group is 70 (40), it's estimated to need 118 subjects in each group by the sample size calculation formula (PASS) of comparing the means of two samples to achieve the power of 90% with  $\alpha = 0.05$  (two-sided), provided that the four groups are designed in a 1:1:1:1 ratio. Considering the dropout rate of 10%, each group is planned to enroll 132 subjects, with a total of 528 subjects.

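### SPID24 is defined with the opposite sign to its planning values, and its 24 h score, a quarter of the time weight, can be taken after the pump has stopped

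*Combined protocol and SAP*

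**What the plan says.** **Sign.** Protocol 7.1 states that "The difference from baseline PI score will be recorded as PID", and its worked example subtracts the baseline score from each later score. SAP 7.3.1 repeats the example, including "PI_2 - PI_0) \times (2-1) + (PI_1 - PI_0) \times (1-0.5". The SAP's general rule agrees: in 7.1.4, change from baseline "is defined as the test value at follow-up visit after treatment - baseline value". Both documents use an NRS on which larger numbers mean more pain. Protocol 10.1 and SAP 2.4 take a mean SPID24 of 88 (SD 45) for the low dose and assume that "the mean (standard deviation) of SPID 24 in the placebo group is 70 (40").

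**Testing rule.** Protocol 10.3 and SAP 7.1.2 and 7.3.1 test the high dose against placebo first, two-sided at 0.05. They go on to the low dose if that difference is significant. Neither document says in which direction.

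**Timing.** Protocol 2.2 defines the endpoint "up to 24 h after starting infusion of loading dose of investigational product", and the treatment-period headings (protocol 3 and 6.2, SAP 2.3) set 0 h at that start. Protocol 3 nevertheless ends its list of NRS times with "min as the assessment point window for 18 h and 24 h) after the infusion". The 24 h score has a window of plus or minus 20 minutes. For the pump, "The subject will continue using the PCA pump until 24 h", plus or minus 5 minutes. Once the treatment period is over, protocol 5.6 says that "subsequent analgesics and dosages will be at the discretion of the investigator according to the hospital's routine practices", and protocol 5.7 exempts such analgesics from the prohibited list. The imputation rule in SAP 7.1.3 names only rescue parecoxib and rescue sufentanil.

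**The concern.** The primary endpoint should have one sign, and the planning values should share it. Programmed as written, a working drug produces a negative treatment-minus-placebo difference, whereas the plan describes a positive one. SPID6, SPID12, SPID18 and SPID12-24 inherit the same sign, while TOTPAR runs the other way (larger is better), so the efficacy tables would mix directions without saying so. The gate adds to this: taken literally, a high dose significantly worse than placebo would also open the low-dose test.

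The second issue is what the last score measures. SPID24 is meant to describe 24 h on study treatment. No section requires the 24 h score to be taken before the pump stops or before a new analgesic is given. By contrast, the satisfaction scores are explicitly tied to pump stop. A score taken late could reflect analgesia that is neither study drug nor protocol rescue, and SAP 7.1.3 would use it as observed.

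**Working it through.** **1. The plan's own figure.** Inputs from protocol 10.1: difference 88 - 70 = 18; SDs 45 and 40; two-sided alpha 0.05; power 90%; equal groups.

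- Root-mean-square SD = sqrt((45² + 40²)/2) = sqrt(1812.5) = 42.57.
- n = 2 × (1.960 + 1.282)² × 1812.5 / 18² = 117.6, so 118 per group, with power 90.1%.
- 118 / 0.90 = 131.1, so 132 per group; 4 × 132 = 528.

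The stated sample size reproduces. A noncentral-t version with unequal variances gives 89.9% power at 118, which is immaterial.

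**2. Sign.** Under the written formula, SPID24 divided by 24 is the time-weighted mean of PI_t - PI_0.

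- +88 would mean 88/24 = 3.67 NRS points above baseline.
- +70 would mean 70/24 = 2.92 points above baseline.

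Both arms would be worse than at baseline, and the active arm worse than placebo. The planning values make sense only as PI_0 - PI_t. Written with the formula's sign they are -88 and -70, a difference of -18. Since (-18)² = 18², n stays at 118, power at 90.1%, and the two-sided p-value is the same.

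**3. Gate.** Standard error at 118 per group = sqrt((45² + 40²)/118) = 5.54. If the high dose did as well as the plan assumes for the low dose (the documents give no separate value), the chance of a significant result in the wrong direction is about 1 in 10 million. With no true difference it is 2.5%.

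**4. Weight of the 24 h score.** SAP 7.3.1 uses planned times, and the preceding score is at 18 h.

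- Weight = 24 - 18 = 6 h.
- 6/24 = 25% of SPID24; 6/12 = 50% of SPID12-24.

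**5. Windows, counted from 0 h.**

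| Event | Earliest | Latest |
|---|---|---|
| 24 h NRS score | 23:40 | 24:20 |
| Pump stop | 23:55 | 24:05 |
| End of treatment period | 24:00 | 24:00 |

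The longest gap from pump stop to score is 24:20 - 23:55 = 25 minutes. Up to 20 minutes of the window lie after the treatment period.

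**6. Possible size (illustration only).** One NRS point at 24 h moves SPID24 by 6 units, a third of the planned 18. As an assumption, let the effect be even over time: 18/24 = 0.75 points at every score. If the whole between-arm difference at 24 h were lost in all subjects, the planned difference would fall by 6 × 0.75 = 4.5 to 13.5, and power at 118 per group to 68%. With no loss, power stays at 90.1%. The documents do not say where in this range the trial would fall.

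**The case against.** **On the sign.** The formula, the example and the SAP's change-from-baseline rule agree with each other; only the planning values, taken by reference to a foreign study, are positive. The test is two-sided, so nothing in the inference moves. This stands. A reader might infer that the sample size or the primary test is invalid, and the calculation shows that it is not. Fixed-sequence testing with a two-sided hypothesis also controls type I error as claimed, so adding a direction to the gate clarifies the rule rather than repairs it.

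**On the worked example.** It uses only 0.5, 1 and 2 h, although seven scores are scheduled by 2 h. A reader might infer that four scores are to be dropped. The documents do not support that: both present it as an example, the general sum governs, and SAP 7.3.1 calls for the planned time points.

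**On the time origin.** Counting from the end of the roughly 10-minute infusion would move the 24 h window to 23:50-24:30 and the longest gap to 35 minutes. That reading conflicts with the defined 0 h, the endpoint definition and the flow chart, and the synopsis lists the NRS times without the loose phrase. The phrase needs correcting, but the larger gap should not be claimed.

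**On the 24 h score.** The target is 24:00, and the window also allows a score from 23:40 with the pump running. The window is a tolerance, not a distribution of actual times. It is the same in all blinded arms. Pump stop alone may matter little for SHR8554: the phase 1 half-life of 6.08-6.96 h implies a terminal-phase loss of about 4-5% in 25 minutes, although decline soon after a press may be faster. In the placebo arm, stopping saline removes no drug. A reader might go on to assume, say, a 2-point fall after a post-treatment analgesic, but the documents give no figure for such an effect or for how many subjects it would reach. All this limits the size of the point. It does not close the gap in the text.

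**Conclusion.** Both parts hold, within limits.

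The sign contradiction is certain on the text. It reverses the planned difference from +18 to -18, and with it the reported difference (taken as treatment minus placebo) and its confidence interval. It leaves sample size, power and the two-sided p-value untouched. The consequence is confined to how the result is read and to a gate that names no favourable direction.

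The timing gap is also in the text: a score with 25% of the time weight of SPID24 and 50% of SPID12-24 can be taken up to 25 minutes after pump stop, possibly after an analgesic that the imputation rule does not name. Whether this happens, and how often, cannot be known from the documents. The fall in power to 68% rests on an even effect that is wholly lost at that score in everyone, and should not be read as a forecast. Neither sensitivity analysis in SAP 7.5 addresses the issue.

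The point is worth correcting because it concerns the primary endpoint and costs little.

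**What to change.** - In protocol 7.1 and SAP 7.3.1, define PID_t = PI_0 - PI_t and state that a larger SPID favours treatment. State that differences are treatment minus placebo.
- In protocol 10.3 and SAP 7.1.2 and 7.3.1, open the low-dose test only if the high dose is significantly better than placebo.
- State once, and apply throughout, that all assessment times count from 0 h, the start of the loading infusion.
- Reconcile the 24 h assessment window with the pump-stop window and the end of the treatment period, so that the 24 h NRS and pain relief scores reflect the on-treatment state. One way is to close the assessment window at pump stop. No rule on stopping the pump or giving analgesia needs to change.
- Matching the worked example to the scheduled time points is tidying only.

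The cost is wording in both documents, a narrower 24 h assessment window and one instruction to sites. No assessment is added and the sample size stays the same.

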| Data Analysis / Statistical Methods | 
The general principles for descriptive statistical analysis in this study are as follows: Count data will be summarized using frequencies and percentages. Measurement data will be summarized using mean, standard deviation, median, maximum, minimum, etc. Plasma concentration data will be summarized using mean or geometric mean, standard deviation, coefficient of variation or geometric coefficient of variation, median, maximum, and minimum. SAS 9.4 will be used for calculation, and all statistical tests will be performed using two-sided tests, with <math>P \leq 0.05</math> considered as statistically significant.
 
Efficacy Analysis
 
The primary efficacy variable SPID24 will be compared between groups using analysis of variance, and SPID24 in each group will be statistically described. The high dose group and low dose group will be tested sequentially, and descriptive statistics will be performed in the morphine group. For the secondary efficacy variables, analysis of variance, chi-square test, Fisher's exact probability method, and nonparametric test will be used for difference analysis according to the nature of the data.
 
Safety Analysis
 |

|  |                                                                                                                                                                                                                                                                                                                                              |
|--|----------------------------------------------------------------------------------------------------------------------------------------------------------------------------------------------------------------------------------------------------------------------------------------------------------------------------------------------|
|  | 
The incidence of AEs and ADRs in each group will be compared using chi-square test or Fisher's exact probability method, and frequency and percentage will be used to describe the AEs and ADRs.
 
PK Analysis
 
The population PK model parameters (CL, V, etc.) will be estimated using the pharmacometric method.
 |

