### **Efficacy Analysis**

- 1) Time-weighted Sum of Pain Intensity Differences at rest at 6 h, 12 h, 18 h, 12h-24 h, and 24 h (SPID6, SPID12, SPID18, SPID12-24 and SPID24) will be compared between groups using analysis of variance;
- 2) Time-weighted Total Pain Relief at 6 h, 12 h, 18 h, 24 h, and 12-24 h (TOTPAR6, TOTPAR12, TOTPAR18, TOTPAR24, and TOTPAR12-24) will be compared between groups using analysis of variance;
- 3) The time to the first use of rescue analgesics will be compared between groups by nonparametric test;
- 4) Cumulative amount of rescue analgesics from 0 h to 24 h will be compared between groups using analysis of variance;
- 5) The number of treatments of rescue analgesia from 0 h to 24 h, the total number of presses and number of effective presses of PCA pump from 0 h to 24 h will be compared between groups by nonparametric test;
- 6) The percentage of subjects who do not use rescue analgesics from 0 h to 24 h will be compared between groups using chi-square test or Fisher's exact probability method;
- 7) The subject's satisfaction score with analgesic treatment will be compared between groups by nonparametric test;
- 8) The investigator's satisfaction score with analgesic treatment will be compared between groups by nonparametric test.

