## Version History

| SAP Version,
Date  | Protocol
Version, Date | Written/Reviewed
by    | Revision History                                                                         |
|-----------------------|---------------------------|---------------------------|------------------------------------------------------------------------------------------|
| V0.1, 12 Apr
2021  | V2.0, 20 Dec
2020      | [name]/[name] |                                                                                          |
| V0.2, 11 May
2021  | V3.0, 13 Apr
2021      | [name]/[name] | Updated per protocol version 3.0                                                         |
|                       |                           |                           | 1. The pairwise comparison of
quantitative indicators was changed
to group t-test; |
| V0.2, 09 Sept
2021 | V3.0, 13 Apr
2021      | [name]/[name] | 2. Added sensitivity analysis;                                                           |
|                       |                           |                           | 3. Adverse reactions were updated to
"Treatment Related Adverse Events";              |
|                       |                           |                           | 4. Added analysis of drug metabolizing
enzymes in subjects.                           |
| V1.0, 13 Sept
2021 | V3.0, 13 Apr
2021      | [name]/[name] | Version 1.0 finalization                                                                 |

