## 2.8 Modifications to the Statistical Analysis in the Protocol

NA

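### The primary SPID24 t-test leaves out baseline NRS, which costs precision but not validity; adjusting for it is a free improvement, and the protocol and SAP should name the same test

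*Combined protocol and SAP*

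**What the plan says.** SAP 7.3.1 defines SPID as the sum, over planned time points, of the pain score minus baseline, each multiplied by the preceding interval. The high dose is tested against placebo first, then the low dose, each at two-sided 0.05, with the difference and its 95% CI. The test is stated as "A group t-test will be used for the comparison between two groups". No covariate or factor is named.

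Baseline NRS is taken at rest within 5 minutes before the loading dose (protocol, Study Design; SAP 2.3). Its only planned use is in SAP 7.2.3: "Baseline NRS scores: mean, standard deviation, maximum, minimum and median will be used to describe the scores". The two sensitivity analyses in SAP 7.5 change the handling of scores after rescue and the population. Neither adjusts for baseline.

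The protocol names another method. Its synopsis says that SPID24 "will be compared between groups using analysis of variance, and SPID 24 in each group will be statistically described", and its Efficacy Analysis section says of the SPID variables that they "will be compared between groups using analysis of variance". It names no covariate either. The SAP section headed "2.8 Modifications to the Statistical Analysis in the Protocol" is answered NA. The SAP's Version History notes, for a draft of September 2021, "The pairwise comparison of quantitative indicators was changed to group t-test".

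**The concern.** An outcome with baseline built into it at a weight of 24 h carries between-subject variation in starting pain that treatment cannot have caused. An unadjusted test leaves that variation in the error term. It also lets any chance difference in baseline between two arms pass into the estimated effect, multiplied by 24 times one minus the slope of later pain on baseline. Confidence intervals are then wider than they need be, and a modest imbalance would be awkward to explain with no adjusted analysis prespecified. Two documents that name different methods for the primary endpoint, with no note of the difference, invite a question that is easily avoided.

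**Working it through.** **The plan's own sample size.** From the protocol's Sample Size section: means 88 and 70, SDs 45 and 40, two-sided 0.05, power 90%.

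- Pooled SD = √((45² + 40²)/2) = √1812.5 = 42.57.
- n = 2 × 1812.5 × (1.960 + 1.282)² / 18² = 117.56, so 118 per group. An exact noncentral-t calculation gives 119.
- 118/0.9 = 131.1, so 132 per group and 528 in all.

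The stated 118, 132 and 528 are reproduced, and they are right for the unadjusted test.

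**Weight of baseline.** The planned times are 0, about 10 min (end of infusion), 20, 30 and 45 min, then 1, 1.5, 2, 3, 4, 5, 6, 8, 10, 12, 18 and 24 h. The intervals are 3 × 1/6, 2 × 0.25, 2 × 0.5, 4 × 1, 3 × 2 and 2 × 6 h, which sum to 0.5 + 0.5 + 1 + 4 + 6 + 12 = 24 h. Apart from sign, SPID24 = 24 × PI₀ minus the weighted sum of later scores.

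**What adjustment would gain.** Let b be the slope of the time-weighted mean later score on baseline, and S the SD of baseline NRS. Both are assumptions. The slope of SPID24 on baseline is 24(1 − b), so r = 24(1 − b)S/42.57. The residual SD is 42.57 × √(1 − r²). Power at 118 per group is Φ(18/(residual SD × √(2/118)) − 1.96).

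| b | S | r | R² | Power at 118 |
|---|---|---|---|---|
| no adjustment | – | – | 0 | 90.1% |
| 0.4 | 1.0 | 0.34 | 11.4% | 93.2% |
| 0.4 | 1.2 | 0.41 | 16.5% | 94.4% |
| 0.6 | 0.8 | 0.18 | 3% | – |
| 0.2 | 1.5 | 0.68 | 46% | – |
| 0.8 | 1.0 to 1.2 | 0.11 to 0.14 | 1.3% to 1.8% | about 90.5% |
| 1.0 | any | 0 | 0 | 90.1% |

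In the two central rows 1/(1 − R²) is 1.13 and 1.20, equivalent to 13% to 20% more patients.

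**Simulation** (20,000 runs per setting, 118 per arm). Type I error of the unadjusted t-test was 0.049 to 0.053 for baseline correlations from 0 to 0.6. At correlation 0.5, power was 0.894 for the t-test and 0.962 for ANCOVA.

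**Chance imbalance.** A baseline difference of 0.2 points with b = 0.4 shifts the contrast by 24 × 0.6 × 0.2 = 2.9 units, or 16% of the planned 18. With S of 1.0 to 1.2 the standard error of the baseline difference is S × √(2/118) = 0.13 to 0.16. An imbalance at least that large, in either direction, therefore occurs in about 12% to 20% of comparisons.

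**The two test names.** Analysis of variance on two groups is the equal-variance t-test. In a simulated example F = 17.096 = t², with the same p-value. If the error were pooled over four arms (SDs 45, 45, 45 and 40), simulated power was about 0.89 against 0.90, and type I error about 0.045 against 0.050.

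**The case against.** The strongest reply is that nothing here is wrong. Randomization makes the unadjusted comparison unbiased. The planning SDs of 45 and 40 already contain the baseline variation, so 90% power is reached without a covariate. The 2.9-unit shift is about half of the contrast's standard error (42.57 × √(2/118) = 5.54), and the t-test's interval already allows for it. The gain rests on two quantities that the documents do not supply, and it disappears as the slope nears 1. All of this stands. It sets the size of the point but does not remove it.

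One feature of the SAP argues against a slope near 1. SAP 7.1.3 sets scores missing during night sleep to 3, so the difference is then 3 minus baseline and depends on baseline alone. The 18 h and 24 h scores each carry 6 h, a quarter of the endpoint. How many scores this touches cannot be known from the documents.

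A reader might infer that the conflict between analysis of variance and t-test leaves the confirmatory p-value undefined. The documents do not support that. The protocol leaves detailed methods to an SAP finalized before database lock, that SAP names one test, and both documents share the hypotheses and testing order. Nor does the Version History line by itself prove a departure from the protocol, since it describes a change between SAP drafts. The gap appears only when the current protocol is set beside the current SAP 7.3.1 and 2.8.

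A reader might also conclude that surgical approach must be a covariate. Both laparotomy and laparoscopy are eligible, but the documents give no figure for its effect on SPID24, and neither the study procedures nor SAP 7.2.3 shows that it is recorded.

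**Conclusion.** The primary analysis is valid but less efficient than the data allow. Under the central assumptions (baseline SD 1.0 to 1.2, slope 0.4), adjusting for baseline NRS removes 11% to 17% of the variance and adds 3 to 4 points of power at 118 per group. The plausible range is wide, and the gain can be close to nothing. Baseline imbalance here is a matter of chance, so it would be a mistake to read the point as bias, inflated type I error or an undersized trial. The mismatch between protocol and SAP is a matter of record-keeping with little numerical consequence.

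**What to change.** Make the primary analysis an ANCOVA of SPID24 with treatment and continuous baseline NRS. State whether it is fitted to all four arms or to each pair. Report the two placebo contrasts in the existing high-then-low order, with LS-mean differences and 95% CIs. Use the same model for SPID6, SPID12, SPID18 and SPID12-24. Keep the t-test as a sensitivity analysis and state its variance assumption, since the planning SDs differ. Add surgical approach only if it is recorded for every subject.

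Bring the protocol's analysis of variance and the SAP into line, and replace NA in SAP 2.8 with a short statement of the change.

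The cost is wording in the two documents, settled before unblinding. Baseline NRS is already collected, no subjects or visits are added, and simulated type I error of the ANCOVA stayed at 0.049 to 0.051.
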